## Abstract

Primary dysmenorrhea (PD) is a painful menstruation that can persist for the duration of a woman’s fertile life. Non-steroidal anti-inflammatory drugs, hormonal therapy, physiotherapy techniques, etc., are the main treatments. The main objective of this study is to evaluate the effectiveness of transcutaneous posterior tibial nerve stimulation (TTNS) in PD patients. The study will consist of a single-blind randomized clinical trial, parallel-assigned with two arms. Women with PD (18–43 years) with regular menstrual cycles and at least 4 points in VAS will be randomly divided into experimental (TTNS) and placebo (simulated stimulation) groups during 12 treatment sessions (1 session/week) and several follow-ups: monthly during treatment and 1, 3 and 6 months after. Maximum and mean pain intensity, pain duration, pain severity, number of anti-inflammatory drugs, quality of life, sleep quality, overall improvement, treatment satisfaction and secondary effects will be measured once a month every 6 months and at 3 and 6 months. The Student’s *t*-test for independent samples or the Mann–Whitney U test will be used. The literature shows effective physiotherapeutic techniques for PD in the short term, which do not act on causes and have limitations. The TTNS technique can be used in transcutaneous and percutaneous modalities, with similar effectiveness, but the transcutaneous causes less discomfort. TTNS modulates pain, and long-term benefits could be achieved at low cost and without patient discomfort.

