The posterior tibial nerve (L4–S3) has the same medullary levels as the hypogastric sympathetic plexus (L4–L5) and the pelvic parasympathetic plexus (S2–S4). Its stimulation produces impulse rebalancing in these centers, as is the case with the posterior tibialis relationship with the voiding centers [36,37]. Through that stimulation, uterine myometrium contractions are reduced; pain is alleviated by the decrease in uterine hypercontractility. This reduction in pain improves quality of life and sleep.

The main objective of this study is to verify whether posterior tibial nerve transcutaneous stimulation improves pain, quality of life and sleep deficiency in patients with PD in the short, medium and long term.

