## 2. Materials and Methods

### 2.1. Objectives

#### 2.1.1. Main Objective

To prove the Effectiveness of TTNS Treatment for PD in the Short, Medium, and Long Term

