### 2.2. Hypothesis

#### 2.2.1. The General Hypothesis Is That

The Application of TTNS Results in Decreased Pain during Menstruation, and An Improvement in Quality of Life and Sleep Deficiency

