### 2.8. Data Analysis

For the statistical analysis, the corresponding statistical tests will be carried out to establish the differences between groups and differences within each group independently. 

The results will be expressed as mean ± standard deviation for the quantitative variables and as a number and percentage for the qualitative variables. Normality will be evaluated with the Kolmogorov–Smirnov test. The mean of the two groups will be compared using a Student’s *t*-test for independent samples or a Mann–Whitney U test as appropriate. Qualitative variables will be analyzed using an x^2^ test. The relationships of the quantitative variables to each other will be tested using the Pearson or Spearman correlation as appropriate. To analyze the effect of the intervention, the results obtained among the intervention group will be compared with those obtained among the control group. A value of *p* < 0.05 will be established as statistically significant.

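### No outcome or time point is named as the confirmatory comparison, and no rule says whether any or all results at p < 0.05 would establish effectiveness.

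*Protocol article*

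**What the plan says.** All references are to the Protocol article.

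- **Main aim, section 1 (Introduction).** The aim is to verify whether TTNS "improves pain, quality of life and sleep deficiency in patients with PD in the short, medium and long term". That is three domains by three horizons.
- **Main objective, section 2.1.1.** "To prove the Effectiveness of TTNS Treatment for PD in the Short, Medium, and Long Term". The three horizons remain, but no outcome is named.
- **General hypothesis, section 2.2.1.** "The Application of TTNS Results in Decreased Pain during Menstruation, and An Improvement in Quality of Life and Sleep Deficiency". The domains are joined by a conjunction, with no decision rule attached.
- **Secondary objectives, section 2.1.2.** Pain, sleep and quality of life appear again, each once for the short term and once for persistence. NSAID reduction, satisfaction and adverse reactions are added.
- **Measures.** The Abstract lists "Maximum and mean pain intensity, pain duration, pain severity, number of anti-inflammatory drugs", which gives five pain-related variables. Section 2.5.2 adds eight SF-36v2 dimensions without singling one out, and section 2.5.3 adds the PSQI total.
- **Analysis, section 2.8.** "The mean of the two groups will be compared using a Student’s" t-test for independent samples, or a Mann–Whitney U test. Within-group tests and correlations are also planned. The section bases the effect of the intervention on the comparison of the two arms. The only error rate given is the 5% threshold, p below "0.05 will be established as statistically significant".
- **Sample size, section 2.4.** Sixty participants, tied to no outcome, so a primary outcome cannot be inferred from it.

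**The concern.** A 5% threshold holds the error rate of a claim at 5% only when one identified test carries that claim. Here the claim is broad and no single test carries it. The hierarchy is also muddled: the domains that define the main aim in section 1 and the hypothesis in section 2.2.1 return in section 2.1.2 as secondary objectives. Nothing is then tested by the main objective alone.

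Two things are at stake. First, the error rate of the main claim is undefined, because it depends on a success rule that is not written. Second, with the rule open, the headline outcome and visit can be chosen after the data are seen. One favourable quality-of-life dimension at one visit could be reported as success. The main objective is worded as proof, so a positive result could not be read as confirmatory.

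**Working it through.** **The plan's own figure.** The only error-rate figure is the 5% threshold. One test at 5% gives 1 − 0.95 = 0.05, which agrees. No family-wise error rate, power or effect size is stated, so there is nothing further to reproduce.

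**Inputs from the document.**
- Alpha 0.05 (section 2.8). Sidedness is not stated; two-sided is assumed.
- Three domains × three horizons = 9 tests (section 1).
- Measures: 5 pain + 8 SF-36v2 + 1 PSQI = 14 (Abstract, sections 2.5.2 and 2.5.3).
- Visits: about three monthly assessments on treatment plus three afterwards = about 6 (schedule in the Abstract), so 14 × 6 = 84 tests.
- Sixty participants at 1:1 (sections 2.4 and 2.3) = 30 per arm.

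**Assumed.** The document gives no correlations. The values below, between outcomes and between times, are assumptions.

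**Independent tests, no true effect, any significant result counts.** The chance of at least one false positive is 1 − 0.95^m:
- m = 3 (horizons only, as in section 2.1.1): 1 − 0.95^3 = 14%
- m = 9: 1 − 0.95^9 = 37.0%
- m = 84: 1 − 0.95^84 = 98.7%, with 84 × 0.05 = 4.2 expected false positives

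Counting only results that favour TTNS, each test contributes 2.5%: 1 − 0.975^9 = 20.4%, and 1 − 0.975^84 = 88.1%.

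**Correlated tests.** Two-sided t-tests were simulated with 30 per arm and 10,000 to 20,000 replicates. The correlation of different outcomes at different times was taken as the product of the two values shown.

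| Correlation (outcomes / times) | 9 tests, either direction | 9 tests, favouring TTNS | 84 tests, either direction | 84 tests, favouring TTNS |
|---|---|---|---|---|
| 0 / 0 | 37% | 20% | 99% | 88% |
| 0.3 / 0.5 | 31% | 16% | 93% | 63% |
| 0.5 / 0.5 | 30% | 15% | 86% | 51% |
| 0.5 / 0.7 | 26% | 13% | 78% | 42% |
| 0.7 / 0.7 | 23% | 11% | 64% | 33% |
| 0.8 / 0.8 | 19% | 10% | 47% | 23% |

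**The all-must-succeed reading.** If every domain had to be significant, a false claim would need a false positive in each, so the domains would add no inflation to the 5%. The conjunction in section 2.2.1 permits this reading, but no section states it as a rule.

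**Cost of blanket adjustment.** With 30 per arm and 80% power, the detectable standardised difference is (z for alpha + z for power) × √(2/30):
- alpha 0.05: (1.960 + 0.842) × 0.2582 = 0.72
- Bonferroni over nine, alpha 0.05/9 = 0.0056: (2.773 + 0.842) × 0.2582 = 0.93

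At an assumed difference of 0.73, power falls from 81% to 52%. Naming one comparison avoids this loss.

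**The case against.** **An analysis plan may exist, and an article condenses the protocol.** Adjustment methods and testing order can reasonably sit in an analysis plan, so their absence is not the point. Which outcome and time point carry the main claim is a protocol decision. The article does state its objectives and hypothesis, and none of them settles it. If an unseen document names a primary comparison, these sections still conflict with it.

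**The objectives have some structure.** Section 2.1.2 separates short-term effects from confirmation that they persist, which suggests that persistence is conditional on an earlier gain. NSAID reduction appears only as a secondary objective. This stands as a caution against treating every horizon and measure as an equal route to success. It is not a formal hierarchy.

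**A reader might infer that the trial is very likely to find effectiveness somewhere even if TTNS does nothing.** The documents do not support this. The three-by-three structure gives at most 37%, and at most 20% for results favouring TTNS. Figures near certainty need all 84 tests to count, with low correlation. No section says that the 84 define the main claim. Zero correlation is implausible for maximum and mean scores from one diary, or for repeated measures in the same women.

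**Within-group and correlation tests might seem to add further routes to the claim.** They do not. Section 2.8 rests the intervention effect on the between-arm comparison, and correlations among variables cannot show effectiveness. They are left out of every count above.

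**Conclusion.** The point holds in this form: no confirmatory comparison is designated, no any-or-all rule is given, and one unadjusted 5% threshold serves every test. On the any-result reading, the chance of at least one false positive over nine tests is 37% if independent and about 19% to 31% under the assumed correlations. For results favouring TTNS it is about 10% to 20%, against the 2.5% that a single two-sided 5% test allows in that direction.

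Counting all 14 measures at six visits raises the two-sided figure to about 47% to 99%. That is an upper case, driven by the assumed correlation. These sizes rest on two-sided testing, 30 per arm, no dropout and the any-result reading. An all-domains rule would remove the inflation from the domains. The document's silence between the two rules is itself the defect.

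**What to change.** Before unblinding, name one confirmatory between-arm comparison at two-sided 5%: one pain outcome, either at one time point or averaged over a stated period. Maximum VAS adjusted for the two-cycle baseline is one example; other choices would serve equally well.

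Treat all other outcomes and visits as secondary. Either test them in a prespecified order, or report them as estimates with 95% confidence intervals and no confirmatory claim. The particular order is the sponsor's choice.

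Align the aim in section 1, the objectives in sections 2.1.1 and 2.1.2, the hypothesis in section 2.2.1 and the analysis in section 2.8, so that the same comparison is primary throughout.

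No extra participants, visits or data are needed. Because the main objective of an ethics-approved, registered trial changes, this is a protocol amendment and not an edit of wording alone. If the primary comparison fails, no confirmatory claim can be made for the outcomes outside it.

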### 2.9. Ethical Considerations

The study was approved on 12 December 2019, by the Ethics Committee for Drug Research, Valladolid East Health Area, of the Hospital Clínico Universitario de Valladolid, located at Hospital Clínico Universitario de Valladolid, [name]. The research will follow Helsinki and CONSORT guidelines and all participants will be informed and sign an informed consent to participate. The study has a ClinicalTrials.gov, accessed on 21 May 2023, registration number ID: NCT04896814.

## 3. Discussion

Dysmenorrhea is currently postulated as one of the health problems that most affect the quality of life of women, with repercussions on their working life. In addition, physiotherapy is very present today and treatments are emerging with the aim of improving pain and the quality of life of patients with urogynecological complications [31,32,46].

There are numerous studies in the literature about physiotherapy treatments which try to relieve menstrual pain [13,14,16,17,21,22]. There is considerable heterogeneity in the studies published related to physiotherapeutic treatments, with studies referring to manual therapy techniques, thermotherapy, cryotherapy, neuromuscular taping, therapeutic exercise and different electrotherapy techniques. Within the interventions related to electrotherapy, where the presented technique would be encompassed, the most used technique is TENS [13,14,47]. These studies compared the use of TENS for 3 months with a control group in a population of nulliparous and multiparous women of childbearing age, a sample similar to the presented study. Only one of the studies [47] did not allow the use of contraceptives and the other two studies allowed the use of NSAIDs. In the present study, women who have not used contraceptives or have an IUD implanted will be included, since in this case it is considered that it would be difficult to discriminate which effects could be attributed to the medication and which to the treatment applied in the study. On the other hand, the intake of NSAIDs is considered appropriate since it is taken as an indicator of pain improvement. As for the measurement tools, the vast majority of studies take the VAS as a reference for pain assessment, and statistically significant differences were observed when comparing between groups in the short-term decrease in pain [13,14,47]. Furthermore, in the study by Hai-Yan et al. [13], a statistically significant decrease in NSAID intake was observed when comparing both groups. On the other hand, two of the studies [13,14] did not show statistically significant improvements in the experimental group with respect to quality of life. Long-term follow-up is not observed in the studies presented, which is essential to understand the duration of the effects of the technique.

However, many limitations have been found in the reviewed publications, with low methodological quality. Likewise, it is observed that the treatment techniques used in these studies have been proposed to combat pain secondary to the underlying pathology and not to the cause itself, obtaining short-term results [8,13,21].

Posterior tibial nerve stimulation has been studied as a treatment for chronic pelvic pain with beneficial results in reducing pain and improving quality of life [32,33,34,35], although the literature analyzed is scarce and samples observed in studies are very small. 

In these studies, middle-aged men and women with a diagnosis of chronic non-cyclic pelvic pain of more than 6 months’ duration, in which PD was not found, were included. Although PD is considered a chronic pelvic pain, it is necessary to differentiate it from other non-cyclical pathologies such as endometriosis, interstitial cystitis, etc. Most of the intervention groups consisted of 12 weeks of treatment at the rate of one 30 min session per week of percutaneous application, inserting the needle 3–6 cm cephalad from the medial and posterior malleolus to the tibia bone and with a neutral electrode placed in the same leg in the plantar arch of the foot, by unilateral application. Stimulation parameters of 20 Hz frequency and 200 µs pulse duration and intensity at the motor contraction threshold were used. In the present study, the same application modality will be used, although it was decided to perform it bilaterally in order to increase the therapeutic effects and by transcutaneous application. The technique has been used over time in two variants, transcutaneous (using surface electrodes) and percutaneous (using needles). Most studies have used the percutaneous modality, but other studies have demonstrated similar transcutaneous modality effectiveness, with a discomfort reduction that patients feel when being stimulated [48,49]. All studies have suggested improvement in short-term pain, assessed with the VAS and/or the SF-MPQ. Regarding quality of life, some studies have assessed it using the SF-36 questionnaire, finding positive changes in some domains for the experimental group in the short term. However only one study [35] conducted long-term follow-up, which suggested that the technique is still effective 6 months after the end of its application, which would lead to an improvement of pain in the medium-long term. This is an interesting aspect of the present study, in which a long-term follow-up will be carried out up to 6 months post-treatment.

Finally, no studies addressing the treatment of PD using this technique have been found.

## 4. Limitations

The sample required to carry out the study requires very specific inclusion and exclusion criteria, which could limit the planned sample size.

Although it is not the aim of the present study there are no tools for measuring the rate of prostaglandins or uterine contractility.

## 5. Conclusions

The technique of transcutaneous stimulation of the posterior tibial nerve in its percutaneous modality could be considered as an alternative treatment for primary dysmenorrhea without adverse effects for women. This technique could be a useful, effective and safe tool for the treatment of women with primary dysmenorrhea improving pain, quality of life and sleep, and reducing work absenteeism.

## Figures and Tables

**Figure 1 healthcare-11-01633-f001:**
[figure not shown]
CONSORT flow diagram.

## Data Availability

All data will be available under reasonable request to the corresponding author.
